## Abstract

**Background:**

Obesity is a growing problem worldwide, especially in countries with improved socioeconomic circumstances. Also, in the Netherlands the incidence of overweight and obesity is rising. There is increasing evidence on the association between obesity and tumorigenesis. Of all cancer types, endometrial cancer (EC) has the strongest positive correlation with obesity. Obesity is generally defined as a body mass index (BMI) >30, yet does not cover the differences in fat distribution in visceral and subcutaneous compartments. Visceral fat is assumed to be relatively more metabolically active and likely negative prognostic biomarker in non-endometrioid EC. Whereas subcutaneous fat is mainly responsible for oestrogen production through increased aromatase activity.

**Objective:**

The aim of this study is to compare hormone levels and inflammatory markers after bilateral salpingo-oophorectomy (BSO) in obese and non-obese patients. Secondary objectives are to compare the effect of fat distribution and diagnosis (benign vs. EC) on the observed changes in hormone levels and inflammatory markers, and to compare the effect of BSO on menopausal complaints.

**Methods:**

Prospective multicentre observational cohort study. A total of 160 patients will be included, of which 80 patients with a normal BMI (18–25 kg/m2) and 80 patients with an obese BMI >32–35 kg/m2. Preoperative abdominal CT will be performed and fasting venous blood samples are obtained for hormone levels and inflammation markers analysis. During surgery, adipose tissue biopsies of subcutaneous and visceral (omental and intestinal epiploic fat) compartments will be collected and stored fresh frozen. In addition a fasting blood draw six weeks after surgery will be obtained. All subjects will fill in two questionnaires before surgery and one after surgery.

**Discussion:**

We hypothesize that BMI, the type of fat distribution, and possibly the underlying pathology significantly influence in hormone levels, and systemic inflammation changes after BSO. Previous studies have found several clues for a relationship between obesity and endometrial cancer. We expect that our study will contribute to pinpoint the exact differences between ‘healthy obesity’ and ‘unhealthy obesity’ and will help to identify patients that are more at risk of developing cancer (or possibly suffer from other related problems such as cardiovascular problems e.g.).

## Introduction

Obesity is a growing problem worldwide, especially in countries where socioeconomic circumstances improve [1]. In the Netherlands the incidence of overweight and obesity is rising [2]. From the 1990s the percentage of people with a body mass index (BMI) of 25–30 kg/m2 has risen from 24.4% up to 32.4%, and people with a BMI > 30 has more than doubled from 5.6% to 12.1% [2]. Obesity is related to many diseases, including diabetes and cardiovascular disease [3, 4], there is also increasing evidence on the association between obesity and tumorigenesis. The underlying mechanisms linking obesity to cancer development are complex and may not be identical in all tumour types [5, 6]. There are three main hypotheses linking obesity to the development of cancer. 1; Endogenous sex-steroids production, 2; chronic hyperinsulinemia, and 3; systemic inflammation [5, 6] Fig 1. Considering all cancer types, endometrial cancer (EC) incidence has the strongest positive correlation with BMI [7–9]. With every 5 BMI units the risk of EC increases 50% [9]. In EC, long-term unopposed oestrogen stimulation has been established to play a causative role, especially in the aetiology of the endometroid subtype.

**Fig 1 pone.0276516.g001:**
[figure not shown]
Three main hypotheses for the development of endometrial cancer in obese women.

Adipose tissue is a very complex endocrine organ that produces adiponectin, leptin, and also steroid hormones. In premenopausal women the ovaries are the main source of oestrogen production [10–12]. However, after menopause, the subcutaneous adipose tissue is the most important producer of oestrogens due to the presence of aromatase, which converts androgens to oestrogens [13]. This mechanism of the production of endogenous sex-steroids plays an important role in the development of EC. Furthermore, obesity-mediated inflammation and insulin resistance have also shown to be important in this process [5, 6, 14]. Chronic hyperinsulinemia, which is common in obese women, has an effect on cell proliferation directly by high insulin levels and indirectly by higher levels of circulating insulin growth factors (IGFs). The chronic inflammation in obese patients results in a higher level of leptin (anti-apoptotic and pro-angiogenetic) and a lower level of adiponectin which as a result promotes cell proliferation and inhibits cell death. These three mechanisms are thought to play an important role in the development of EC [4, 5].

The chronic hyperinsulinemia and systemic inflammation possibly also explains why also for the non-endometrioid subtype, the incidence rate is positively associated with weight gain [15, 16].

Obesity is defined by the world health organisation as a BMI >30 [17]. BMI is a simple, and clinically easily applicable indicator, yet does not cover the complexity of fat distribution in visceral- and subcutaneous compartments, nor the ratio between muscle tissue and fat tissue [16, 18]. Internationally the importance of fat distribution is gaining more attention [19–21].

Previous study showed that a higher visceral fat percentage was a negative prognostic biomarker in non-endometrioid EC (NEEC) [19] compared to subcutaneous fat which is important for oestrogen production through increased aromatase activity [20, 22, 23]. Fat distribution can be measured by imaging methods like CT and MRI or estimated by measurements of skinfolds, DXA-scan and hip-waist circumference. The latter divides women into two groups, women with an apple figure who presumably have more visceral fat and women with a pear figure who most likely have more subcutaneous fat. The MRI an CT related measurements can distinguish between subcutaneous and visceral adipose tissue [5]. Adipose tissue compartments, determined by CT segmentation scans, have been correlated to systemic hormone levels, tumour inflammation and pathway activation in a number of studies [19–22]. In the light of the differences between adipose tissue in the various compartments, the relative increase in central obesity (visceral obesity) through the menopausal transition is of potential additional importance [24].

Through the rising prevalence of obesity worldwide, it is expected that the EC incidence will continue to rise [1, 15, 25, 26]. In the more affluent countries, EC is the most frequent gynaecological malignancy [27, 28]. The primary treatment of EC consists of hysterectomy with BSO. Removal of ovaries serves three goals: 1, it is part of the staging procedure of EC; 2, to exclude the chance of concurrent ovarian cancer and 3, it leads to reduction of the remaining oestrogen and androgen production and thus possibly reduces risk of recurrence. It is uncertain to what extent the sex steroid hormone (and inflammatory) levels drop after BSO, especially in obese women with endometrial cancer. Removal of the ovaries demonstrates to what extent oestrogen production is or was driven by the ovaries or the adipose tissue compartment. Pinpointing this more specifically will help in further understanding the role of adipose tissue in the development of EC.

## Materials and methods

### Study design

This is a prospective observational cohort study. Patients will be recruited from four hospitals including two academic hospitals (academic hospital Maastricht (AZM) and Radboud university medical centre (Radboudumc)) and two large teaching hospitals (Canisius Wilhelmina Ziekenhuis (CWZ) and VieCuri). Inclusions started from 1st of September 2021 in AZM and Radboudumc and inclusions at CWZ and VieCuri will start in 2022. As of this moment the study is actively recruiting. The ethics committee of aZM/UM, Maastricht, approved the study protocol for all participating hospitals, which was registered under NL76255.068.21. All participants will provide written informed consent.

### Objective/aim

The aim of this study is to compare hormone levels and inflammatory markers after BSO in obese and non-obese patients. Secondary objectives are to compare the effect of fat distribution and diagnosis (benign vs. endometrial cancer) on changes in hormone levels and inflammatory markers after BSO in obese and non-obese patients, and to compare the effect of BSO on menopausal complaints. We hypothesize that obese post-menopausal women will still have relatively high circulating concentration of oestrogen, especially women with a high subcutaneous fat percentage.

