### Sample size

There are no previous studies with comparable analysis, allowing for a formal sample size calculation. Therefore, we have taken the difference in hormone level as the starting point for a sample size calculation. Based on an expected difference of 20% in hormone level changes between lean and obese patients (decrease in hormone levels of 70% in lean, and 50% in obese after BSO), using a 90% power and alpha 0.05, 154 patients are required for the primary objective of this study [29]. We have chosen to include 160 women, 80 obese and 80 non-obese. The gap in BMI between the 2 groups (7/10 BMI points) increases the likelihood to obtain significant differences in hormone- and inflammation marker levels.

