### Stratification

We strive to include a safety margin of 5–10% per stratum to allow for missing data. In both cohorts, due to a short preoperative waiting list (<4 weeks) it is not expected any patients are included whose data or tissue is not subsequently used. For this study, we can optimally compare the included participants using our 20/20/20/20 distribution. Using a population-based inclusion, we would likely have too low numbers in some groups to allow for meaningful analyses. However, as a consequence the external validity is somewhat reduced.

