### Statistical analysis

Variables will be analysed quantitatively (CT derived markers, hormones and inflammatory markers) or qualitatively (menopausal symptoms) and stratified by menopausal status and BMI. Comparison of characteristics and study variables will be performed using Chi squared tests (categorical data) and Mann Whitney U test or student t-test (continuous variables, depending on normality of distribution). Correlations will be assessed using Spearman’s rank correlation. Study-related, the oncological patients will be followed for three years for disease recurrence and/or disease-related death. Additionally, correlations between inflammatory markers in adipose tissue and circulating oestrogen levels after treatment and outcome are observed.

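### The secondary objective compares the effects of diagnosis and fat distribution in obese and non-obese women, but no named method estimates or tests a difference in effect between the BMI groups

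*Protocol article*

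**What the plan says.** The Objective/aim section of the protocol article gives, as a secondary objective, a comparison of the influence of fat distribution, and likewise of "diagnosis (benign vs. endometrial cancer) on changes in hormone levels and inflammatory markers after BSO in obese and non-obese patients". The abstract's Objective paragraph has the same objective without the BMI clause: "compare the effect of fat distribution and diagnosis (benign vs. EC) on the observed changes in hormone levels and inflammatory markers".

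The Statistical analysis section says that variables are analysed "stratified by menopausal status and BMI". It then names the methods:
- for categorical data: "Comparison of characteristics and study variables will be performed using Chi squared tests (categorical data";
- for continuous data: "Mann Whitney U test or student t-test (continuous variables, depending on normality of distribution";
- for associations: "Correlations will be assessed using Spearman’s rank correlation".

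No model with more than one factor is named, and no comparison of an effect between strata.

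The design is built for comparison between groups. The Sample size section states "We have chosen to include 160 women, 80 obese and 80 non-obese", and the Stratification section states "we can optimally compare the included participants using our 20/20/20/20 distribution".

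**The concern.** Whether diagnosis acts differently in obese and in lean women is a question about a difference between two differences. A t-test or Mann-Whitney test of cancer versus benign, done within one BMI group, estimates the effect in that group only. A Spearman coefficient between a fat measure and a hormone change does the same. Two such results side by side do not give the contrast between them, its uncertainty or a test of it.

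The objective is therefore left without a stated analysis. The gap could be filled by reading a significant result in one BMI group and a non-significant result in the other as evidence of a BMI-specific effect. That step has no controlled error rate, because it depends on the power within each group.

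**Working it through.** **Plan's own figure.** The article gives no effect size, SD, power or error rate for the diagnosis comparison, so there is nothing to reproduce. Its figure of 154 patients concerns the primary lean-versus-obese comparison and does not bear on this point.

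**Inputs**
- 80 obese and 80 non-obese women (Sample size).
- Cells of 20/20/20/20 (Stratification). Assumption: these are menopausal status by diagnosis within each BMI group, which gives 40 cancer versus 40 benign per BMI group.
- Alpha 0.05 (Sample size), taken as two-sided.
- Assumption: the true cancer–benign difference is d SD, the same in both BMI groups. The article gives no value, so a range is shown.

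**Step 1: power in one BMI group.** This is the two-sample t-test with n = 40 per arm, noncentrality d × √(40/2) and 78 degrees of freedom. Call the power p.

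**Step 2: chance that exactly one of the two BMI groups is significant.** The groups are independent, so this is 2p(1 − p). As the true effect is the same in both, every such split is misleading if it is read as a difference in effect.

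| d (SD) | p | 2p(1 − p) |
|---|---|---|
| 0 | 0.050 | 9.5% |
| 0.2 | 0.143 | 25% |
| 0.3 | 0.263 | 39% |
| 0.44 | 0.494 | 50% |
| 0.5 | 0.598 | 48% |
| 0.6 | 0.755 | 37% |
| 0.8 | 0.942 | 11% |
| 1.0 | 0.993 | 1.4% |

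For example, at d = 0.5: 2 × 0.598 × 0.402 = 0.481. The maximum of 2p(1 − p) is 50%, reached at p = 0.5.

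**Step 3: the direct test.** A test of the BMI group by diagnosis interaction has a 5% false-positive rate by construction, whatever the common effect. Simulation with 20,000 replicates per setting gave 4.7–5.2%.

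**Step 4: precision of the direct estimate.** With four cells of 40, the standard error of the difference in effects is SD × √(4/40) = 0.316 SD. The 95% CI half-width is 1.96 × 0.316 = 0.62 SD. Power to detect a true difference in effects is about 35% at 0.5 SD and 88% at 1.0 SD.

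No error rate was worked out for the fat-distribution part. The same gap exists there: one correlation per BMI group, with no comparison between them.

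**The case against.** Five points can be made for the plan.

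1. **The article never says that significance will be compared across strata.** This stands. A reader might infer that the plan will produce BMI-specific claims that are mostly chance. The documents do not support that: the step is not stated, and the share of false claims would depend on how often effects truly differ, which is unknown.

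2. **An error rate of about half is not general.** This also stands. It is the ceiling of 2p(1 − p), reached only near 50% power per group. The rate is about 10% with no effect and about 1% with a large one. Effect size and cell sizes are both assumptions.

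3. **Stratified by BMI may partly mean grouped by BMI.** If every test stayed within a BMI stratum, the primary lean-versus-obese comparison could not be done. Stratum tests also yield estimates and intervals, not only p-values, and these could be compared. This is fair, but the article names no such comparison.

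4. **The abstract allows a main-effect reading.** For that reading, a two-group test and a correlation are ordinary tools. This stands as an ambiguity. The Objective/aim section is the fuller statement, however, and it includes the BMI clause. Recruiting both diagnoses within each BMI group in balanced cells fits the between-group question.

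5. **Model terms are commonly left to an analysis plan that is not shown.** This would answer a complaint about missing detail. Here the article has its own analysis section that chooses methods, and those methods do not answer the objective it states.

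**Conclusion.** The point holds as a mismatch between a stated secondary objective and the methods named for it. Nothing named estimates or tests whether the effect of diagnosis or fat distribution differs between obese and non-obese women.

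The risk from comparing significance across strata is conditional. With 40 versus 40 per BMI group and an identical effect in both, the results would split in anything from about 1% to 50% of studies, depending on the assumed effect, and in 37–50% for effects of 0.3–0.6 SD. The interaction test stays at 5%. The primary objective is not affected.

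**What to change.** - Align the abstract and the Objective/aim section on whether a comparison of effects between BMI groups is intended. If only the overall effect of diagnosis and fat distribution is meant, drop the BMI clause.
- If the comparison is intended, replace the stratum-by-stratum tests for this objective with one linear model of the change (log scale if skewed). Its terms are BMI group, diagnosis, menopausal status and BMI group × diagnosis.
- For fat distribution, use a parallel model with BMI group × CT fat measure.
- Report the difference in effect with its 95% CI, and state that no BMI-specific effect will be claimed from separate stratum p-values.

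**Cost.** Only the analysis wording changes; the model uses data already planned, and the article describes the study as still recruiting. The downside is that the interaction estimate is imprecise, at about ±0.62 SD with four cells of 40. A null result would therefore not exclude a moderate difference, and the report should say so.

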### Participants (Fig 2)

**Fig 2 pone.0276516.g002:**
[figure not shown]
Schematic display of participants. Total number of participants is 160 women.

In total 160 patients will be included, of which 80 patients with a normal BMI between 18–25 kg/m2 and 80 obese patients with BMI ≥35 kg/m2 (WHO obesity class 2). In both these groups an even number of peri-/premenopausal women and postmenopausal women are included, and women with endometrial cancer (EC) and/or atypical endometrial hyperplasia; cases, and women with a benign adnexal pathology (including but not limited to adnexal enlargement/abnormality); controls will be included. Patients will be included pre-operatively. In case of a final diagnosis being ovarian malignancy, this participant will be excluded and a patient with a benign diagnosis included instead.

### Exclusion criteria

Exclusion criteria for this study are another malignancy in the 5 years prior to inclusion (with the exception of basal cell carcinoma), use of systemic hormonal therapy <3 months prior to inclusion, insufficient understanding of the Dutch language, patients not allowed to undergo CT-scan, patients who are expected to be offered HRT immediately after surgery.

### Sample size

There are no previous studies with comparable analysis, allowing for a formal sample size calculation. Therefore, we have taken the difference in hormone level as the starting point for a sample size calculation. Based on an expected difference of 20% in hormone level changes between lean and obese patients (decrease in hormone levels of 70% in lean, and 50% in obese after BSO), using a 90% power and alpha 0.05, 154 patients are required for the primary objective of this study [29]. We have chosen to include 160 women, 80 obese and 80 non-obese. The gap in BMI between the 2 groups (7/10 BMI points) increases the likelihood to obtain significant differences in hormone- and inflammation marker levels.

### Data collection schedule (Fig 3)

**Fig 3 pone.0276516.g003:**
[figure not shown]
Schematic display of content and timepoints (T) for data collection during the study period. Three time points for patients with benign disease (T1-T3) and four time points (T1-T4) for patients with endometrial cancer (EC).

At three (women with benign diagnoses) or four (women with EC) different time points data will be collected from the subjects.

At timepoint 1 (T1), a physical examination is conducted where hip and waist circumference are measured and patient variables including age, height, weight, BMI, history, cumulative illness rating scale (CIRS) and menopausal status collected. Furthermore, routine abdominal CT imaging will be performed in all patients. Finally, patients are requested to answer a validated questionnaire, the Green climacteric scale enquiring into presence of menopausal symptoms, and are asked to answer three questions on their physical activity level.

At timepoint 2 (T2) subjects will undergo the clinically indicated surgical procedure. At start of surgery, a fasting blood draw will be obtained to measure oestrogen levels and systemic inflammation markers. During surgery subcutaneous adipose tissue and visceral adipose tissue (fat apron and intestinal epiploic fat) as well as tumour (where applicable) will be collected, and snap frozen.

At timepoint 3 (T3) 4 to 6 weeks postoperatively, another fasting blood draw is obtained for measurement of oestrogen levels and systemic inflammation markers. In case of a recent infection the blood draw will be postponed until 10 days after the end of the infection. In case of adjuvant therapy, the postoperative blood draw will be performed latest at start of the adjuvant therapy. Finally, subjects will be asked to fill in the Green climacteric scale questionnaire a second time.

For subjects with the diagnosis of EC clinical follow-up data will be collected during 3 years (T4).

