### Data analyses

Using the abdominal CT-scans, abdominal fat volumes will be segmented and quantified using a semi-automatic dedicated software (iNtuition, TeraRecon Inc. San Mateo, CA, USA) [20, 30]. This allows quantification of subcutaneous abdominal fat volume (SAV), visceral abdominal fat volume (VAV), total abdominal fat volume (TAV) and visceral fat percentage (VAV% = [VAV/TAV] x100). Hormone levels (locally in the adipose and tumour tissue and systemically in the blood) will be measured by Liquid-Chromatography-tandem-Mass-Spectrometry (LC-MS/MS) analysis and compared pre- and postoperatively. The biospecimens will be temporarily stored prior to use in this study at the MUMC Biobank [31]. In the Biobank Information System (BIS) type, date and volume of each specimen is recorded. A selection of steroid hormones including oestrogens, androgens, progestogens and corticosteroids as well as local adiponectin, resistin, leptin will be determined in the collected adipose tissue. Inflammatory markers both locally in fat tissue (macrophages, T cells: TNF-α, IL-6, and IL-1β) and systemically (blood) (including C-reactive protein (CRP), interleukin 1 beta (IL1β), interleukin 6 (IL6), tumour necrosis factor alpha (TNFα), insulin-like growth factor 1(IGF1)), will be determined. Samples will be further characterised by omics technologies (genomics, transcriptomics, proteomics and metabolomics). Generated data will be used for biomarker discovery, this data will be used to explore the cellular pathways underlying the various patient characteristics. Furthermore, we will analyse the effect of CT derived fat distribution markers on hormonal/inflammatory activity in different corresponding fat samples.

Pre- and postoperative questionnaires will be analysed and compared. The Green climacteric Scale, assessing menopausal complaints, can be divided into three subcategories; psychological, physical and vasomotor complaints [32]. We will assess all three subcategories separately to evaluate if there are any differences in the groups of patients (pre vs. postmenopausal and obese vs. non-obese patients).

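### The postoperative draw is timed in two ways, and its shift rules let time since surgery differ by diagnosis and screen infection at only one end of the change score

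*Protocol article*

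**What the plan says.** The Abstract (Methods) gives a single time: "In addition a fasting blood draw six weeks after surgery will be obtained". The Data collection schedule gives a window: "At timepoint 3 (T3) 4 to 6 weeks postoperatively, another fasting blood draw is obtained".

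The schedule then adds two rules for T3:

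- Infection: "In case of a recent infection the blood draw will be postponed until 10 days after the end of the infection".
- Adjuvant treatment: "In case of adjuvant therapy, the postoperative blood draw will be performed latest at start of the adjuvant therapy".

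The baseline sample (T2) is taken at the start of surgery. The T2 paragraph has no infection rule.

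The markers measured at both ends are listed under Data analyses: "systemically (blood) (including C-reactive protein (CRP), interleukin 1 beta (IL1β), interleukin 6 (IL6), tumour necrosis factor alpha (TNFα" and IGF1. They serve two aims. The main one is "The aim of this study is to compare hormone levels and inflammatory markers after BSO in obese and non-obese patients". The other is "Secondary objectives are to compare the effect of fat distribution and diagnosis (benign vs. endometrial cancer) on changes in hormone levels and inflammatory markers".

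The Statistical analysis section names two-group tests and stratification by menopausal status and BMI. It does not mention time since surgery. Data analyses says that the biobank system records the date of each specimen.

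**The concern.** A before-and-after change can be compared between groups only if both samples are taken under the same conditions in each group. Here the later sample has two stated times. One of the rules that moves it depends on having cancer, and the other depends on infection.

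If an inflammatory marker is still changing in the weeks after surgery, a group drawn earlier will show a different change for that reason alone. The benign-versus-EC comparison is the most exposed, because the adjuvant rule acts on one side of it only.

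The infection rule shows that the authors regard recent infection as distorting the postoperative markers. The same distortion at baseline would enter the change score with the opposite sign, and no rule is stated for it.

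**Working it through.** The plan gives no figure on this point to reproduce. The check sets its statements side by side. The arithmetic that follows is illustrative and rests on assumed inputs.

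**1. The two timings.** Six weeks is day 42; 4 to 6 weeks is day 28 to day 42. The single time is the upper end of the window, so a site following the schedule may draw up to 14 days before the time in the Abstract.

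**2. Who the adjuvant rule can reach.** Participants defines cases as EC and/or atypical hyperplasia and controls as benign adnexal pathology. It replaces women whose final diagnosis is ovarian malignancy. Exclusion criteria removes most women with another malignancy in the previous 5 years. In practice that leaves only EC women for adjuvant therapy. The rule is an upper limit: it moves a draw only when therapy starts before the draw would otherwise be taken, and it takes a draw below day 28 only when therapy starts before day 28. No earliest day is stated.

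**3. Conflict between the rules.** Let E be the day the infection ends, A the day adjuvant therapy starts and D the day of the draw. The infection rule needs D ≥ E + 10. The adjuvant rule needs D ≤ A. No day satisfies both when A < E + 10, and no precedence is given. The infection rule also leaves the window whenever E + 10 > 42, that is E > 32, with no latest day stated.

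**4. One-sided infection screen.** Change = T3 − T2. The 10-day rule is stated for T3 only.

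**5. Possible timing gap by diagnosis (assumed inputs).** Mean gap = share drawn early × (usual week − early week).

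- Smallest: 0.20 × (5 − 4) = 0.2 weeks.
- Largest: 0.40 × (6 − 3) = 1.2 weeks.

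**6. Possible timing gap by BMI (assumed inputs).** Mean gap = (infection share in obese − share in lean) × delay.

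- Smallest: (0.10 − 0.03) × 1 = 0.07 weeks.
- Largest: (0.30 − 0.05) × 3 = 0.75 weeks.

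**7. What a timing bias would do to a test.** Assume 80 per group. This is the stated BMI split; it is also the diagnosis split if the 20/20/20/20 distribution means four menopause-by-diagnosis cells in each BMI group. With a bias of b standard deviations, δ = b/√(2/80) = b/0.158, and the two-sided error is 1 − Φ(1.96 − δ) + Φ(−1.96 − δ).

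- b = 0.05: about 6%
- b = 0.1: about 10%
- b = 0.2: about 24%
- b = 0.3: about 48%

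Nothing in the article links a gap in weeks (steps 5 and 6) to a value of b (step 7).

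**The case against.** The strongest reply is that this is a wording slip plus a sensible safeguard. Six weeks lies inside the 4 to 6 week window, and the schedule, not the Abstract, is the operative text. The infection rule keeps acute infection out of CRP and IL-6. Covariates, sample flags and rule precedence may stand in a full protocol or analysis plan that is not shown.

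Much of this is fair. Leaving time since surgery out of the named tests is not in itself a fault of the article. What stands is what the article itself states: two different times, two rules that cannot always both be met, and an infection rule written for one of the two samples. An analysis plan can adjust for the sampling day, but it cannot redraw a sample.

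A reader might infer more in three ways. The documents do not support any of them.

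- **That residual surgical inflammation does bias the comparison.** Nothing in the article says how long surgical inflammation lasts. If the excess halved every 7, 10 or 14 days (assumption), a day-28 draw would carry 2^(14/7) = 4, 2^(14/10) = 2.6 or 2^(14/14) = 2 times the residual of a day-42 draw. Those ratios say little about size: the shares of the initial excess left are 6.3% v 1.6%, 14% v 5% and 25% v 12.5%. The largest ratio goes with the smallest absolute gap. They also compare single draws at the two ends of the window, not group means.
- **That the BMI comparison is distorted.** This needs more infections in obese women, which the article does not state. Read as in step 7 of the working, the 20/20/20/20 distribution gives both BMI groups equal numbers of cases and so largely shields that comparison from the adjuvant rule. The shield is incomplete, because the mix of EC and atypical hyperplasia among cases is not fixed by BMI.
- **That EC women have the larger operation.** The Introduction says "The primary treatment of EC consists of hysterectomy with BSO", but no text says that women with benign disease have less extensive surgery.

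**Conclusion.** The point holds in a limited form. The Abstract and the Data collection schedule give different times for the same draw and must be reconciled. The adjuvant rule can make time since surgery differ by diagnosis, and this can confound the secondary benign-versus-EC comparison of inflammatory change. The infection rule leaves the T2 baseline uncovered and can conflict with the adjuvant rule.

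The size and direction of any confounding are unknown. The gap of 0.2 to 1.2 weeks rests on assumed adjuvant shares and draw times, and turning it into bias needs the further assumption that the markers are still changing at that time. An effect on the BMI comparison is a possibility only. The sample size rests on hormone change, and no bias in the hormone comparison is claimed here.

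The point is worth acting on because the specimen dates are already recorded and the remedy costs little.

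**What to change.** 1. State one T3 window, in the same words in the Abstract and the Data collection schedule.
2. State which T3 sampling rule prevails when the infection and adjuvant rules cannot both be met, and flag the affected samples. This concerns the sample only and leaves the start of treatment alone.
3. Flag recent infection at T2 as well as T3, without changing the timing of surgery. Repeat the inflammatory change analysis without flagged samples.
4. Compute days since surgery from the specimen dates: T2 is drawn at surgery, so it is the T3 date minus the T2 date. Report the inflammatory comparisons by diagnosis, and by BMI, adjusted for it or restricted to in-window samples as a sensitivity analysis.

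The cost is a few lines of wording, an infection flag at T2 and slightly more analysis. A few samples drop out of the sensitivity analyses, possibly unevenly by diagnosis or BMI, so the numbers left out should be reported by group. Early draws forced by adjuvant therapy will remain; the fix makes them visible and tests their influence but does not remove them.
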